**Fig. 3 Fig3:**
[figure not shown]
Schematic illustration of the exposure session

### Procedure and design

The trial takes place at the Department of Clinical Psychology and Psychotherapy at Saarland University. It includes seven phases: initial screening and diagnostic phase, randomization, (pseudo)-biofeedback training, practice at home, exposure to spider video clips, post-assessment and follow-up assessments. For a detailed temporal overview see the Standard Protocol Items: Recommendations for Interventional Trials (SPIRIT) Figure (Fig. 4). The SPIRIT Checklist is provided as Additional file 4.

**Fig. 4 Fig4:**
[figure not shown]
Standard Protocol Items: Recommendations for Interventional Trials (SPIRIT) Figure of the current trial

#### Screening and diagnostic phase

Participants who volunteered to take part in the trial are contacted by phone for a short screening using the SAS [33]. Participants scoring 14 or higher are invited to complete an online questionnaire administered via SoSci Survey [53], which consists of the STAI-T, the FSQ, the PHQ-D, the ASI-3, the BDI-II and three questions on the perceived self-efficacy in handling spiders. If participants reach a FSQ score of 50 or higher, they are asked to attend an assessment at the Department of Clinical Psychology and Psychotherapy. This first assessment takes about 45 min and contains the ADIS section “Specific Phobias” and the BAT. Both are administered by a trained member of the research team. Participants with an avoidance score of at least three and a fear score of at least four are invited to take part in the biofeedback training.

#### Randomization

The randomization process using a generated list is conducted by a member of the research team who is not involved in the data collection process. Participants are allocated to one of the four aforementioned experimental groups (*n* = 20 per group): (1) group 1 (G1, HRV/HRV); (2) group 2 (G2, HRV/pseudo); (3) group 3 (G3, pseudo/pseudo); and (4) group 4 (G4, pseudo/−).

#### Biofeedback training

The biofeedback training session starts with a resting phase of 5 min to assess baseline HRV. Afterwards, participants complete the STAI-S. Then, depending on the experimental group, the training session starts. All participants receive two types of training, each lasting 30 min. The order of both training parts is randomized within every group. After each type of training, participants complete the STAI-S again to evaluate their current anxiety level.

#### Practice at home

At the end of the training session, all participants receive an audio file for home training. The version of the provided file depends on the participants’ individual resonance frequency (G1 and G2) or takes the form of a standard audio file for both pseudo-biofeedback tasks (G3 and G4). Participants are asked to continue the training for 6 days (20 min a day).

#### Exposure session

The exposure session is conducted one week after the initial training session in the same laboratory using the same technical devices. All exposure sessions take place in the afternoon (between 2 p.m. and 6 p.m.) to control for diurnal cortisol levels, which can influence exposure effects [49]. At first, all participants complete the STAI-S. Then participants go on to conduct exposure. G1 receives HRV biofeedback during exposure, whereas G2 and G3 are presented with pseudo-biofeedback (task A). G4 has no additional task during exposure.

#### Post assessment

Subsequent to the exposure session, the post assessment takes place: participants complete the STAI-S, the FSQ and the ASI-3. Again, they answer three questions on their perceived self-efficacy in dealing with a spider and the post-exposure BAT is performed.

#### Follow-up assessments

One week and one month after the exposure session, participants are contacted by the research team and asked to complete an online version of the FSQ and to answer the questions on self-efficacy in handling a spider.

### Data collection and statistical analyses

Questionnaire data is registered using SoSci Survey [53] and exported as a .csv file. The BAT results are noted in an Excel sheet by a member of the research team. Further, behavioral data concerning the training and exposure sessions is collected using the E-Prime software and physiological data is stored as a text file using the BFS. All statistical analyses will be conducted by a member of the research team, who was not involved in the data collection process, using IBM SPSS version 24 [54]. The alpha level will be set to *p* < 0.05. The main hypotheses will be tested using a mixed analysis of variance (ANOVA) with group as the between-subjects factor and time (pre assessment, post assessment, follow-up one week, follow up four weeks) as the within-subjects factor. All analyses will be reported with partial *η*^*2*^ as the effect size.

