Regarding the effectiveness of HRV biofeedback, a recent meta-analysis based on clinical and non-clinical samples reports beneficial effects of HRV biofeedback as a stand-alone intervention on symptoms of stress and anxiety [22]. HRV biofeedback significantly reduces stress and anxiety symptoms (*g* = .81) and is superior to various control conditions such as waiting list of sham biofeedback (*g* = .83). Furthermore, several studies have evaluated the effects of HRV biofeedback as add-on intervention in clinical samples: in posttraumatic stress disorder, a case study and a controlled trial have shown beneficial effects of HRV biofeedback during exposure therapy [23, 24]. Positive results in terms of reduced depression scores and increased HRV have also been shown for patients with depression [25, 26]. Further, a recent pilot study demonstrated a trend towards an increased fear reduction in aviophobia patients who received diaphragmatic breathing training prior to exposure in virtual reality [27]. The training used a frequency of six breath cycles per min, which is equal to the average resonance frequency normally used in HRV biofeedback interventions to maximize individual HRV. Hence, it is plausible to assume that the reported beneficial effects are linked to HRV increase caused by slow diaphragmatic breathing.

Taken together, current evidence suggests that HRV biofeedback may be a useful stand-alone intervention and a promising add-on tool to improve psychotherapy outcomes. However, thus far, there is a lack of randomized controlled trials (RCT) supporting the effectiveness of the intervention. This is critical for two reasons: firstly, testing the effects of a therapeutic add-on in a controlled trial is necessary in terms of advancing evidence-based treatments. Secondly, the effects of HRV biofeedback need to be disentangled from possible effects of working memory (WM) tasks, as different studies demonstrate a positive impact of low-load WM tasks on consolidation and reconsolidation memory processes relevant for memorizing therapeutic input [28, 29]. For example, theories on the mechanisms underlying Eye Movement Desensitization and Reprocessing (EMDR) emphasize the role of eye movements as a low-load WM-demanding task [30, 31]. Performing eye movements during imagery exposure reduces WM capacity, thereby decreasing the vividness and emotionality of the traumatic memory [32].

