### Sample size

The intended samples size was calculated using G*Power 3.1 [39]. An a priori power calculation (*α* = .05, 1 – *β* = .85) based on the weighted mean between-group effect reported by Goessl et al. [22] resulted in a total sample size of 80 participants. Thus, 20 participants per experimental group are recruited to ensure sufficient statistical power.

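### For the FSQ, the four-time mixed ANOVA as classically fitted would discard the valid post-exposure score of anyone who misses one online follow-up, and the sample size carries no stated allowance for this

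*Protocol article*

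**What the plan says.** Under Data collection and statistical analyses, the article commits the main hypotheses to a "mixed analysis of variance (ANOVA) with group as the between-subjects factor". The within-subjects factor is time with four levels: pre, post, one week and four weeks. The software is SPSS 24 and the effect size is partial eta squared.

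The four FSQ values are not collected alike. The post value follows the exposure session directly (Post assessment). For the two later values, "participants are contacted by the research team and asked to complete an online version of the FSQ" (Follow-up assessments). The outcome description of the FSQ makes change to post and change to follow-up the primary measure. The BAT, the other primary outcome, is scored only before and after treatment.

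Under Sample size, the power calculation "resulted in a total sample size of 80 participants", and "20 participants per experimental group are recruited to ensure sufficient statistical power". No attrition rate or inflation is given.

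**The concern.** A classical mixed ANOVA takes one row per participant with one column per time, and a row with an empty column is dropped. A participant with sound pre and post FSQ scores who skips the one-week or the one-month questionnaire therefore leaves the whole FSQ model, including any post-exposure contrast taken from it. The article describes no separate pre-post FSQ test that would keep that person.

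Two things are at stake. The first is power, because the number recruited equals the number the calculation asked for. The second is bias. If more fearful participants, or one arm, answer the online questionnaire less often, their observed post scores are discarded selectively.

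**Working it through.** **Inputs from the article.** Four groups of 20 (Sample size). "An a priori power calculation (*α* = .05, 1 – *β* = .85" and "based on the weighted mean between-group effect reported by" a meta-analysis (Sample size); sidedness and test family are not stated. Background gives two effects: g = .83 against control conditions and g = .81 for symptom reduction. I use .83, the between-group figure.

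**Assumptions.** Each follow-up is missed independently with probability q = 5%, 10% or 15%. Tests are two-sided at .05. Cohen's f = g/2.

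**1. The plan's own figure.** For a one-way ANOVA with four groups, noncentrality λ = f²N and df = 3 and N − 4:
- g = .81 (f = .405): N = 80, power .855.
- g = .83 (f = .415): N = 76, power .853; at N = 80, power .873.

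The figure of 80 is thus reached exactly only with g = .81. Since the test family is unstated, this does not show that 80 is wrong.

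**2. Complete cases.** Per group, n = 20(1 − q)²:
- q = .05: 20 × .9025 = 18.05
- q = .10: 20 × .81 = 16.2
- q = .15: 20 × .7225 = 14.45

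**3. Power on those cases, three readings of the test.**
- Pairwise contrast at one time with pooled error: noncentral t, df = 4n − 4, noncentrality .83 × √(n/2). At n = 20 the noncentrality is 2.625; at n = 14.45 it is 2.231.
- One-way omnibus: λ = .415² × 4n. At n = 20 this is 13.78; at n = 14.45 it is 9.95.
- Between-group test averaged over four times: λ = .415² × 4n × 4/(1 + 3ρ), with assumed correlation ρ from .3 to .7.

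| q | n per group | Pairwise | One-way omnibus | Repeated-measures, ρ = .7 to .3 |
|---|---|---|---|---|
| 0 | 20 | .736 | .873 | .946 to .997 |
| .05 | 18.05 | .691 | .831 | .920 to .993 |
| .10 | 16.2 | .642 | .782 | .884 to .985 |
| .15 | 14.45 | .591 | .725 | .838 to .972 |

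A plain two-group t-test (df = 2n − 2) starts slightly lower, at .725 for n = 20.

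**4. Where the planned .85 is lost.** In the one-way reading at g = .83, power is .853 at 19 per group and .830 at 18. So it falls below plan once 10% of participants have at least one missed follow-up.

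**5. With all available values kept.** A participant with a post score stays in the post comparison whatever happens later, so missed follow-ups alone leave that comparison at 20 per group.

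**The case against.** The strongest reply is that the article states neither listwise deletion nor a completer population, and names no SPSS procedure. Missing-data handling is commonly left to a fuller document, which is not shown here. That stands as a limit: a reader might infer that the plan prescribes a completer analysis, and it does not. But the point concerns the model the article does name, whose default behaviour is to need all four values, and not the absence of a missing-data rule.

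Other stronger readings are also unsupported:
- **High non-response.** No rate is given, and the research team contacts participants for what appears to be a short online questionnaire. The loss is conditional.
- **The whole primary analysis shrinks.** The BAT has no follow-up, so a missed online FSQ cannot remove anyone from its pre-post comparison.
- **Nearly everyone will have pre and post scores.** Randomisation precedes training, home practice and exposure. Anyone lost in that interval has no post score, and a different model would not supply one.
- **Uneven spacing violates sphericity.** Time is categorical in the ANOVA, so spacing alone is no violation, and SPSS offers standard corrections.

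The power figures also depend on an unstated test. Pairwise power is already 74% with nobody missing, which is a separate matter. Under the repeated-measures formula, power stays at about .84 or higher even at the largest assumed loss. This limits the size of the power argument but does not remove the discarded data or the possible bias.

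**Conclusion.** The point holds for the FSQ only, and as a conditional risk. The named model, fitted in the usual way, ties the post-exposure FSQ result to response at two later online questionnaires, and the sample size has no stated margin for that. Under the assumed 5%, 10% or 15% independent non-response per follow-up, 18.1, 16.2 or 14.5 complete cases per group remain. Power falls from 74% to 69%, 64% or 59% for a pairwise contrast, and from .873 to .831, .782 or .725 for a one-way omnibus test. The fall is smaller for a test averaged over the four times. The rates, their independence, f = g/2 and the correlations are assumptions. The direction and size of any bias cannot be derived from the article. A change is worth making because a better model is available in the software already chosen.

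**What to change.** For the FSQ, replace the mixed ANOVA with a linear mixed model (SPSS MIXED, REML):
- **Outcome:** FSQ at post, one week and four weeks.
- **Fixed effects:** group, time, group-by-time and baseline FSQ.
- **Covariance:** unstructured across the three times.
- **Population:** all randomised participants with any post-baseline FSQ value, in their allocated group.
- **Contrasts:** group comparisons at post and at both follow-ups, since the FSQ outcome is defined at all of them.

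This model is valid if missingness depends only on observed data, a weaker condition than the complete-case analysis needs in general.

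The cost is a change of analysis wording, with no extra participants or visits. Partial eta squared, promised for all analyses, is not a direct output of this model, so adjusted mean differences with confidence intervals would be reported for the FSQ. Recruitment was still open when the manuscript was submitted (Trial status), so on that timetable the change could precede the analysis.

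Keeping the ANOVA and recruiting more is dearer. At the assumed rates, 80/(1 − q)² gives 89, 99 or 111 participants before rounding to equal groups, and selective loss would remain.

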**Methods:**

Eighty spider-fearful individuals participate in the study. All participants receive a training session in which they practice two tasks (HRV biofeedback and a motor pseudo-biofeedback task or two motor pseudo-biofeedback tasks). Afterwards, they train both tasks at home for 6 days. One week later, during the exposure session, they watch 16 1-min spider video clips. Participants are divided into four groups: group 1 practices the HRV biofeedback and one motor pseudo-task before exposure and utilizes HRV biofeedback during exposure. Group 2 receives the same training, but continues the pseudo-biofeedback task during exposure. Group 3 practices two pseudo-biofeedback tasks and continues one of them during exposure. Group 4 trains in two pseudo-biofeedback tasks and has no additional task during exposure. The primary outcome is fear of spiders (measured by the Fear of Spiders Questionnaire and the Behavioral Approach Test). Secondary outcomes are physiological measures based on electrodermal activity, electrocardiogram and respiration.

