#### Subjective ratings – outcome

##### Fear of Spiders Questionnaire

The FSQ ([36]; German version: [33]) is not just used as a screening tool, but also for outcome assessment. Differences in FSQ scores from pre to post treatment and to follow-up are used as the primary outcome measure.

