#### Behavioral test

##### Behavioral Approach Test

To test participants’ fear and avoidance behavior towards real spiders, the Behavioral Approach Test (BAT; [48]) is employed. The BAT (as administered in a prior study by Lass-Hennemann and Michael [49]) consists of the following procedure: standing in front of a closed room that contains a house spider (*Tegenaria atrica*) measuring about 5 cm (legs included). The spider is placed in a sealed plastic container on a table at the end of the room. Next, if possible, the participant enters the room, approaches the container, removes the lid, inserts a hand and tries to pick up and hold the spider for at least 20 s. When the participant has reached for, or touched, the spider, or when they decide to stop approaching, the remaining distance is noted. In detail, 13 steps are coded: 0 = test room is not entered; 1 = stops 5 m from the container, 2 = stops 4 m from the container; 3 = stops 3 m from the container; 4 = stops 2 m from the container, 5 = stops 1 m from the container, 6 = stops close to the table with the container, 7 = touches the container, 8 = removes the lid, 9 = puts a hand in the container, 10 = touches the spider with one finger, 11 = holds the spider less than 20 s, 12 = holds the spider for at least 20 s. Differences from pre to post treatment are used as a primary outcome measure.

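### The prescribed four-level time factor cannot be applied to the Behavioral Approach Test, a primary measure taken only before and after exposure

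*Protocol article*

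**What the plan says.** All references are to the protocol article.

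- **Primary outcome** (Abstract, Methods): "The primary outcome is fear of spiders (measured by the Fear of Spiders Questionnaire and the Behavioral Approach Test".
- **FSQ endpoint** (Fear of Spiders Questionnaire, under the outcome ratings): "Differences in FSQ scores from pre to post treatment and to follow-up are used as the primary outcome measure".
- **BAT endpoint** (Behavioral Approach Test): "Differences from pre to post treatment are used as a primary outcome measure".
- **First BAT** (Screening and diagnostic phase): "This first assessment takes about 45 min and contains the ADIS section “Specific Phobias” and the BAT".
- **Second BAT** (Post assessment): "the post-exposure BAT is performed".
- **Follow-ups at one week and one month** (Follow-up assessments): participants are "asked to complete an online version of the FSQ and to answer the questions on self-efficacy in handling a spider". The BAT is not among the items.
- **Time factor** (Data collection and statistical analyses): the section names "time (pre assessment, post assessment, follow-up one week, follow up four weeks) as the within-subjects factor". It belongs to the only model that the section gives, a mixed ANOVA for the main hypotheses in which the four groups are compared. No separate model or time factor is given for the BAT.

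**The concern.** The three hypotheses are about reduction in fear. Since the abstract defines fear of spiders by both the FSQ and the BAT, the rule for testing the main hypotheses covers the BAT as well. That rule names four occasions, and the BAT exists at only two of them. It needs a test room and a live spider in a container, so an online follow-up cannot supply it.

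Two things are at stake. First, whoever analyses the BAT must depart from the written rule for a primary measure, and more than one departure is reasonable. A group by two-level time ANOVA and a baseline-adjusted comparison of post-exposure scores both use the same pre and post data and can give different p-values. Second, a model with two follow-up levels suggests that persistence of the effect is tested for the primary outcome as a whole. It can be tested only on self-report.

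**Working it through.** **Step 1: schedule against model.**

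| Time level in the stated model | FSQ collected | BAT collected |
|---|---|---|
| Pre | yes (online screening questionnaire) | yes (first assessment) |
| Post | yes | yes |
| One week | yes (online) | no |
| Four weeks | yes (online) | no |
| Levels available | 4 of 4 | 2 of 4 |

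The two missing levels are empty for all participants in all groups. A repeated-measures ANOVA with four levels would have no participant with complete BAT data. A likelihood-based model would not help either, because the data hold no information on those cells.

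**Step 2: degrees of freedom of the group-by-time test.** Inputs: N = 80 participants (Sample size), k = 4 groups (Randomization), m time levels. The formulas are (k − 1)(m − 1) for the numerator and (N − k)(m − 1) for the denominator.

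- As stated, m = 4: 3 × 3 = 9 and 76 × 3 = 228.
- For the BAT, m = 2: 3 × 1 = 3 and 76 × 1 = 76.

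The test with 9 and 228 degrees of freedom can be computed for the FSQ only. These counts assume that all 80 participants are analysed.

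**Step 3: what the BAT data do allow.** With two levels, the group-by-time F test equals a one-way ANOVA on the pre-to-post difference, which is the endpoint that the BAT section names. The alternative is to compare the post-exposure score between groups with the baseline score as covariate: 3 numerator and 80 − 4 − 1 = 75 denominator degrees of freedom. The baseline BAT is taken before randomization, so it is a valid covariate.

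**Step 4: how the two compare.** Assume equal variance σ² at pre and post and correlation ρ between them; the article gives no value for ρ.

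- Error variance of the change score: 2σ²(1 − ρ).
- Error variance after adjustment: σ²(1 − ρ²).
- Ratio, adjusted to change: (1 − ρ²) / [2(1 − ρ)] = (1 + ρ)/2.

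For ρ = 0.3, 0.5 and 0.7 the ratio is 0.65, 0.75 and 0.85. Under this assumption the adjusted analysis has the smaller error variance for any ρ below 1.

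**The case against.** The strongest reply is that the article sets the time frame outcome by outcome. The FSQ endpoint runs to follow-up and the BAT endpoint stops at post. Read with those definitions, the analysis sentence can be taken as a list of the trial's assessment occasions, to be used where each measure exists. That gives a group by two-level time ANOVA for the BAT, which can be fitted. Leaving out occasions at which the BAT was never scheduled is forced by the design and is not a choice made on results.

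Much of this stands. A reader might infer that the BAT has no workable primary analysis at all, or that any BAT model would have to be chosen after the data are seen. The documents do not support either reading: the BAT section fixes the endpoint as pre to post, and the analysis section fixes the model family. A reader might also infer damage to the FSQ analysis. There is none, since the FSQ is collected at all four levels. Nor does the article use the word co-primary; it calls the FSQ the primary measure, the BAT a primary measure, and lists both in the abstract.

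It can also be said that a condensed article leaves outcome-specific models to a fuller document. That would excuse silence. Here the analysis section states the time levels explicitly, and what it states does not fit one of the two measures of the primary outcome.

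**Conclusion.** The point holds as an inconsistency of moderate weight. The prescribed four-level model cannot be fitted to the BAT, because two of its four levels are never measured. The pre-to-post endpoint implies a two-level analysis with 3 and 76 degrees of freedom in place of 9 and 228, and the analysis section does not say so. No bias, loss of power or inflated error rate is shown to follow. What follows is an avoidable ambiguity over which pre/post analysis counts for a primary measure, and a missing statement that follow-up conclusions rest on the FSQ alone.

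The conclusion rests on the text of the article. The schedule figure is not shown, but the text describes the follow-ups as online and lists their content.

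**What to change.** In the section on data collection and statistical analyses:

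1. Restrict the four-level time factor to the FSQ.
2. Name one pre/post analysis for the BAT. The minimal correction is a group by time ANOVA with two levels. The preferable choice is the post-exposure BAT score compared between groups with adjustment for the baseline BAT, for the reason in Step 4.
3. State the BAT group comparisons that answer each of the three hypotheses. The section names no contrasts for the FSQ either, so there is nothing to copy across.
4. Say that behavioural conclusions apply to the immediate post assessment, and that conclusions at one week and four weeks rest on the self-reported FSQ.

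The cost is a few sentences. No measurement or visit is added, since both BAT scores are already collected. The trial status section reports recruitment still in progress when the manuscript was first submitted, so at that stage the change could be recorded before analysis.
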